**Methods:**

This is a multicenter, prospective, randomized confirmatory trial comparing navigation-assisted procedures with conventional procedures without navigation assistance. Patients allocated to the intervention group will undergo treatment using Vascular Navigation PAD in addition to a mobile C-arm. A total of 160 patients will be randomized in a 1:1 ratio, with 40 patients per group enrolled at each of the two participating hospitals. The primary endpoint is contrast agent volume. Secondary endpoints include patient radiation exposure, physician radiation exposure, fluoroscopy time, and the number of DSAs performed per intervention.

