## Methods: participants, interventions, and outcomes

### Study setting {9}

The study will be conducted in the tertiary University hospital Augsburg, Germany and the tertiary University hospital RWTH Aachen, Germany. A total of 160 patients will be recruited with equal allocation across sites and study groups.

The study population comprises adult patients with PAD and stenotic lesions in the lower extremities who are candidates for endovascular treatment.

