### Outcomes {12}

#### Primary outcome

Primary efficacy parameter of the study is the final value administered contrast agent volume of a manufacturer iodine (concentration of 300 µg/mL) at the end of the procedure. The value is measured by the local research team.

The mean volume will be compared between the intervention and the control group.

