**Table Tabb:** 

Timepoint	*t* < 0	Enrollment		Post-intervention/discharge
		0	1	2 (end of intervention)
Enrollment				
Eligibility screen	X			
Informed consent	X			
Randomization		X		
Intervention (operation with or without Vascular Navigation PAD)			X	
Assessments				
Baseline characteristics (age, weight, height)	X			
Renal function	X			
Pre-existing condition (diabetes, coronary heart disease)	X			
Contrast agent used				X
Fluoroscopy time				X
Air kerma				X
Dose-area product				X
Procedural time				X
Number of angiography series				X

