### Sample size {14}

It is the aim of this study to determine the investigational device’s ability to reduce the nephrotoxic contrast agent volume required during endovascular procedures of the lower extremities. Existing clinical literature suggests a potential reduction of 30% in the volume of contrast agent when comparing procedures with navigation support to those without it [7, 9]. Additionally, information on usually needed contrast agent during procedures without navigation support is provided by a systematic review [9]. Reported values are as follows:Navigation-supported group = 34.7 ± 13.8 mLNon-navigated group (control):◦ Group 1 = 51.3 ± 26.7 mL [7])◦ Group 2 = 88.31 ± 55.35 mL (systematic review, [10])◦ Group 3 = 81.14 ± 58.68 mL (systematic review, [10])

Based on this clinical literature, the expected mean contrast volume was assumed to be 88.16 mL in the control group and 34.7 mL in the navigation-assisted group, corresponding to an anticipated absolute reduction of 53.46 mL. For sample size planning, a superiority margin of 30% of the control-group mean was prespecified, corresponding to 26.45 mL, which was used as the clinical threshold for superiority and not as the expected treatment effect. Assuming a common standard deviation of 55.27 mL, a two-sided significance level of 0.05, and a power of 90%, the required sample size was calculated for a two-group superiority design with a continuous endpoint.

After allowing for a dropout rate of 10%, 80 patients per group were planned.

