## Assignment of interventions: allocation

### Sequence generation {16a}

Once baseline assessments and patient enrollment are completed, participants will be randomized in a 1:1 ratio using a simple envelope randomization. No dedicated sequence generation is used in this study. The envelopes were prepared by the study office staff and are kept in a container by them following thorough mixing. The envelopes are outwardly identical. The surgeons participating in the study are not involved in the randomization process. Participants will draw their envelope out of a pool of the remaining allocations after enrollment.

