## Statistical methods

### Statistical methods for primary and secondary outcomes {20a}

The primary and secondary endpoints will be summarized as mean ± standard deviation or median, as appropriate. Because contrast agent volume and radiation dose are continuous variables and each participant contributes one observation, group comparisons will be performed using an unpaired two-sample *t*-test if the data are approximately normally distributed. The primary analysis will be conducted according to the intention-to-treat principle.

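### The primary t-test is conditional on the trial's own data looking normal, with no criterion and no alternative; one unconditional, site-adjusted analysis of the mean difference would be better

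*Protocol article*

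**What the plan says.** In the protocol article, the section on statistical methods for primary and secondary outcomes {20a} names the unpaired t-test for comparing the groups, but only "if the data are approximately normally distributed". It covers contrast volume and radiation dose, states no way of judging normality, and names no other test. It also allows endpoints to be summarised by mean and SD or by median.

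Under Primary outcome {12}, the target is fixed: "The mean volume will be compared between the intervention and the control group". Sample size {14} adds a superiority margin of 26.45 mL, and the planning statement begins "Assuming a common standard deviation of 55.27 mL".

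On allocation, the abstract plans 160 patients "with 40 patients per group enrolled at each of the two participating hospitals", and Study setting {9} says "A total of 160 patients will be recruited with equal allocation across sites and study groups". Sequence generation {16a} says that "participants will be randomized in a 1:1 ratio using a simple envelope randomization" and mentions no stratification by site. The participation timeline table lists "Baseline characteristics (age, weight, height"), renal function, diabetes and coronary heart disease before randomization. The stated test uses neither site nor any of these.

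**The concern.** The trial is described as confirmatory, so the reader should know before unblinding which test decides it and which quantity it estimates. Here the choice depends on the outcome data. If the data are judged non-normal, the article leaves the primary test undefined. Someone must then choose one after seeing the data, and a common choice would no longer address the difference in means or a threshold in mL.

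A smaller matter is that the unadjusted test makes no use of the planned balance by site or of baseline information already recorded. That can leave the standard error larger than it need be.

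**Working it through.** **Inputs, all from Sample size {14}.** Assumed means 88.16 mL (control) and 34.7 mL (navigation), expected difference 53.46 mL, margin 26.45 mL, common SD 55.27 mL, two-sided alpha 0.05, power 90%, dropout 10%, 80 per group. Listed literature values: 34.7 ± 13.8 (navigated); 51.3 ± 26.7, 88.31 ± 55.35 and 81.14 ± 58.68 (controls). Evaluable per group: 80 × 0.9 = 72.

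**The plan's own figure.** Testing against the margin, the difference to detect is 53.46 − 26.45 = 27.01 mL. With n = 2 × (z_alpha + z_power)² × 55.27² / 27.01²:
- two-sided 0.05: 88 per group, 98 after dropout;
- one-sided 0.05: 72 per group, 80 after dropout.

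The stated 80 is therefore reproduced only one-sided. That is a separate matter, but it explains why two-sided power against the margin starts below 90% in the last step.

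**1. Do the planning figures fit a normal shape?** Volume cannot be negative. Under a normal distribution the share below zero is Φ(−mean/SD):
- control as planned: Φ(−88.16/55.27) = Φ(−1.595) = 5.5%;
- the three literature control groups: 2.7%, 5.5% and 8.3%;
- the common SD applied to the navigation mean: Φ(−34.7/55.27) = 26.5%.

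The control SD/mean ratios are 26.7/51.3 = 0.52, 55.35/88.31 = 0.63 and 58.68/81.14 = 0.72. Skew is likely, although the article gives no shape.

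**2. How often would a formal check fail?** Assume a 5% Shapiro-Wilk test on a control arm of 72 with mean 88.16 and SD 55.27. By simulation (3,000 runs per shape) the rejection rates are:
- zero-truncated normal: 76%;
- gamma: 97%;
- lognormal: 99.6% to 99.8% over separate runs.

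**3. Does failing matter for the t-test?** With both arms at mean 88.16, SD 55.27 and 72 per group (20,000 runs), type I error is 5.07% for the t-test and 5.06% for Welch, under lognormal and gamma alike. With equal means of 60 mL and unequal SDs of 38 and 20, both tests stay at about 5% to 6%.

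**4. What might a switch do?** Assume the fallback is a Mann-Whitney test. With equal means of 60 mL and SDs of 38 and 20 (8,000 runs), it rejects in about 21% (gamma) to 30% (lognormal). With an SD of 24 in the second arm, which matches the navigated ratio 13.8/34.7 = 0.40, the rates are about 15% and 20%.

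**5. What does omitting site cost?** Suppose arms are balanced within site and the overall SD is 55.27. A site difference D leaves a within-site SD of √(55.27² − D²/4), and the true type I error is 2 × [1 − Φ(1.96 × 55.27 / within-site SD)]. For assumed D of 10, 20, 30 and 40 mL this gives 4.9%, 4.6%, 4.2% and 3.6%. The power loss is 0.2 to 3 percentage points.

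**6. What might adjustment gain?** The adjusted SD is 55.27 × √(1 − R²). The documents give no R², so a range is assumed. Power is for a t-test with 72 per group, two-sided 0.05, and a difference of 27.01 mL (margin test):

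| R² | SD (mL) | Power |
|---|---|---|
| 0 | 55.27 | 83% |
| 0.1 | 52.43 | 87% |
| 0.2 | 49.43 | 90% |
| 0.3 | 46.24 | 94% |

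For a test against zero with the expected 53.46 mL, unadjusted power is already above 99.9%, so there is essentially nothing to gain.

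**The case against.** An unadjusted t-test in a 1:1 randomized trial is valid, and covariates and site terms are commonly left to the analysis plan or full protocol, neither of which is shown. No part of the article promises adjustment, so nothing is contradicted on that side. This stands: the adjustment part is a recommended improvement, not an error.

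Several stronger readings are tempting, and the document does not support them:
- **The normality condition is bound to fail.** This needs a formal test and a particular shape. The article says approximately and names no test; a lenient graphical reading could pass, and a truncated normal is rejected only about three times in four.
- **The planned t-test is unsound.** Step 3 shows that it is not, at this size.
- **Error rates of 21% to 30% apply to this trial.** They belong to a rank test that the article never names, in a constructed scenario.
- **The arms differ fourfold in spread.** That sets a literature SD against a planning SD called common. Against the listed control SDs the ratio runs from 26.7/13.8 = 1.9 to 58.68/13.8 = 4.3.
- **Randomization is stratified by site.** Equal counts by site are planned, but the envelope procedure mentions no strata.
- **Rutherford category and lesion location are collected covariates.** The first appears as an inclusion criterion and the second as a subgroup factor; neither is in the assessment table.

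What the objection does not remove is the condition itself. The article states a rule for the primary test, and that rule depends on the data and is incomplete.

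**Conclusion.** The point holds in a limited form. The primary test is made conditional on the outcome data without a criterion or an alternative, while the article fixes a comparison of means and an mL threshold. The planning figures make it likely, though not certain, that a formal check would fail. Since the t-test or Welch test on means keeps about 5% type I error under the skew considered, the condition brings no protection; its only effect is to allow a data-driven change of test and estimand. How much harm follows depends on the fallback, which is unknown.

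Leaving out site and baseline data is valid, mildly conservative if the planned balance by site is achieved, and less efficient. The gain from including them rests on an assumed R² and on testing against the 26.45 mL margin, which the statistical methods section does not mention. A reader should not infer a known power gain.

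**What to change.** Remove the normality condition for the primary endpoint and prespecify one analysis that is carried out whatever the distribution:
- a linear model of contrast volume on arm, site and a short list of baseline covariates already in the assessment table, such as body weight and renal function;
- Rutherford category and pre-procedure lesion location only if they are on the case report form;
- heteroscedasticity-robust standard errors, reporting the adjusted mean difference with its 95% CI.

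Keep the unadjusted Welch test, and any rank-based or log-scale analysis, as sensitivity analyses. The same model can serve dose-area product, air kerma and physician dose, which now share the same conditional rule.

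The cost is analysis wording only, with no extra patients or visits, provided that the covariates are limited to those already recorded. The one constraint is timing: the covariate list must be fixed before anyone sees outcome data by arm. Recruitment is planned to run until October 2026.

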#### Survey data

The Likert scale values from survey data will be averaged over all surgeons and presented as median and interquartile range.

### Interim analyses {21b}

There will be no planned formal interim analyses of the primary and secondary outcomes, the treatment is given at baseline, and it is not possible to subsequently stop treatment for a given participant.

### Methods for additional analyses (e.g., subgroup analyses) {20b}

A subgroup analysis will be executed on all endpoints based on indication/diagnosis, lesion location, and amount and type of endovascular devices used and placed (e.g., stents).

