### Intervention description {11a}

No specific pre-planning procedures involving patient data are required. Patients will receive treatment according to standard clinical procedures using a mobile flat-panel C-arm. The treating physician will determine the procedural steps, including stenting if indicated. The protocol therefore focuses on the study-specific elements rather than providing a fully detailed description of routine clinical care.

Any steps that deviate from the standard of care are highlighted in bold. The subsequent section delineates, in broad terms, the intraoperative workflow with the trial device during a PAD procedure:The mobile flat-panel system will be started and connected via HDMI with the Brainlab hardware running Vascular Navigation PAD.The patient will be transported to the OR. Patient is under local, regional, or general anesthesia.A vascular sheath will be placed at the surgeon’s discretion.The surgeon will create one or more roadmaps according to the device functionality principle, by capturing DSAs and fluoroscopic images within the Vascular Navigation PAD. This capturing process is within the intended use of the investigational device, but additional to the standard of care at the study site.

Note: Image acquisition is done using a flat-panel angiographic imaging device. Acquisition of those image types is standard protocol during endovascular procedures and therefore does not add additional radiation exposure to the clinical procedure.Optional: The surgeon may mark areas of suspected lesions within the Vascular Navigation PAD.The captured images will be stitched together to generate a vessel tree. Image recognition will suggest anatomical overlap, which the surgeon may manually adjust and must confirm.The created (continuous) roadmap(s) will be used to support the navigation of endovascular tools to one or more lesions. The principle of single-image roadmaps is standard of care.The surgeon will then treat those lesions at their discretion and continue with the procedure as intended.The vascular access will be closed as usual (end of clinical procedure).

Post-operative:All image and video data in relation to the procedure (including preoperative imaging data) will be exported and uploaded to a secure platform.A CRF will be completed for each enrolled patient, and no additional diagnostic tests will be performed as part of the study.

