### Strategies to improve adherence to interventions {11c}

Reasons for non-compliance could include Vascular Navigation PAD failure, surgeon error, failure to communicate correct randomization allocation to the surgeon and OR personnel, and cross-over. The patient could impact compliance if they express a wish to withdraw between randomization and surgical procedure or in the event of death.

To improve adherence, treating surgeons and OR personnel receive annual training in the navigation system PAD in accordance with the German Medical Devices Act. The study documentation, including the randomization information, is brought to the operating room with the patient and reviewed by the surgeon before the procedure begins.

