#### Secondary outcome

The secondary endpoints are:Radiation dose received by patients, quantified in the dose-area product (DAP) (µGy·cm^2^) and cumulative air kerma (Gy)Radiation dose received by the physicians, quantified in microsievert (µSv) measured with a personal dosimeter worn at the chest above the lead apron vestQualitative assessment of the device ability to enable navigation of endovascular devices to defined targets in PAD procedures using a 5-point Likert scale

All data shall be recorded by the OR team at the time of the procedure immediately after the sheath is removed.

In addition, the influence on the procedural time in minutes, number of DSAs, fluoroscopy time in minutes, and consumables per lesion shall be noted.

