### Concealment mechanism and implementation {16b} {16c}

Allocation concealment for all participants is ensured by using sequentially numbered opaque envelopes. All envelopes are prepared at the beginning of the study by a study nurse not involved in the inclusion and randomization of the patients.

Patients will be enrolled to the study by their treating physician and randomization will be performed post-consent. Participants will be randomized to Vascular Navigation PAD group or standard imaging techniques in a ratio of 1:1 post-consent and confirmation of eligibility.

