## Assignment of interventions: blinding

### Blinding {17a}

Due to the nature of the intervention, it is not possible to blind the surgeon and outcome assessor. After randomization, the study team is aware of the allocation.

Emergency unblinding is not required in this study.

The data statisticians will be blinded to treatment allocation. The datasets from the two groups are handed over to the statisticians in a blinded manner for primary statistical analysis.

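### Subgroups defined by devices actually used and placed are set after randomisation by an unblinded surgeon, so arm comparisons within them are open to bias and are not randomised comparisons

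*Protocol article*

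**What the plan says.** The section on additional analyses {20b} of the protocol article states: "A subgroup analysis will be executed on all endpoints based on indication/diagnosis, lesion location, and amount and type of endovascular devices used and placed", with stents as the example. The wording of the last factor, "amount and type of endovascular devices used and placed (e.g., stents", refers to devices actually used, not to a pre-procedure plan, and the analysis covers all endpoints. Nothing in the article restricts the factor to planned use or labels these subgroups descriptive.

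Other sections fix when, and by whom, this factor is determined:

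- Timing of allocation (Concealment mechanism and implementation {16b} {16c}): "Participants will be randomized to Vascular Navigation PAD group or standard imaging techniques in a ratio of 1:1 post-consent and confirmation of eligibility". The participation timeline {13} also places randomisation before the operation.
- Who decides on devices (Intervention description {11a}): "The treating physician will determine the procedural steps, including stenting if indicated". In the workflow for the navigation arm, once the roadmap is in use: "The surgeon will then treat those lesions at their discretion and continue with the procedure as intended".
- Knowledge of allocation: under Blinding {17a}, "it is not possible to blind the surgeon and outcome assessor". Under adherence {11c}, the randomisation information goes to the operating room and is "reviewed by the surgeon before the procedure begins".
- A related quantity is also recorded as something the system might influence. The section on secondary outcomes ends with a list of procedural measures: "fluoroscopy time in minutes, and consumables per lesion shall be noted".

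**The concern.** Randomisation makes the arms comparable overall, and within strata fixed before allocation. It gives no such assurance within strata formed by what happened afterwards. Suppose navigation changes how often a stent or a further device is used, or in which patients. Stented navigation patients and stented controls are then different kinds of patients. A more complex case plausibly needs both more devices and more contrast, so the difference within a stratum mixes the effect of the system with a difference in case mix.

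The affected result is any statement that the system saves more or less contrast or radiation in patients who received a given number or type of device. Because the plan applies the factor to all endpoints, the issue recurs for contrast volume, patient dose and physician dose alike. Indication and lesion location do not share the problem if they are taken from information recorded before allocation.

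**Working it through.** **1. Order of events.** Consent and eligibility, then randomisation, then the surgeon reviews the allocation, then the procedure with or without navigation, then devices chosen at discretion. The stratifying factor comes last, after allocation and after the allocated imaging has been applied. This step needs no arithmetic and is enough to show that the strata are not fixed by randomisation.

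**2. The plan's reference figures (Sample size {14}).** Margin: 0.30 × 88.16 = 26.45 mL. Expected effect: 88.16 − 34.7 = 53.46 mL. Both reproduce. The SD is 55.27 mL.

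**3. Illustration of size.** These assumptions are not in the documents:

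- There is no true effect on contrast.
- Case complexity Z is standard normal and has correlation a with contrast volume.
- A patient is stented when a propensity L, which has correlation b with Z, exceeds an arm-specific cut-off.
- 50% are stented in control, and 40% or 30% with navigation.

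For stent rate p with cut-off c, the mean propensity is φ(c)/p among stented patients and −φ(c)/(1−p) among unstented patients:

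| Stent rate | Stented | Unstented |
|---|---|---|
| 50% | 0.399/0.5 = 0.798 | −0.798 |
| 40% | 0.386/0.4 = 0.966 | −0.386/0.6 = −0.644 |
| 30% | 0.348/0.3 = 1.159 | −0.348/0.7 = −0.497 |

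Gaps between arms (navigation minus control):

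- 50% v 40%: 0.168 stented, 0.154 unstented.
- 50% v 30%: 0.361 stented, 0.301 unstented.

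Spurious difference = a × b × gap × 55.27 mL.

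*Complexity fully determines stenting (b = 1), a from 0.3 to 0.7:*

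- 50% v 40%, stented: 0.3 × 0.168 × 55.27 = 2.8 mL, rising to 0.7 × 0.168 × 55.27 = 6.5 mL.
- 50% v 30%: 6.0 to 14.0 mL stented, 5.0 to 11.7 mL unstented.

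*Looser link (a = 0.6, b from 0.3 to 0.7):*

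- 50% v 40%, stented: 0.18 × 0.168 × 55.27 = 1.7 mL, rising to 0.42 × 0.168 × 55.27 = 3.9 mL. Unstented: 1.5 to 3.6 mL.
- 50% v 30%: 3.6 to 8.4 mL stented, 3.0 to 7.0 mL unstented.

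A simulation of the looser model with 2 million patients per scenario agrees: 1.6 to 4.0 mL and 3.0 to 8.4 mL across the two strata. It also shows three further things:

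- With 50% stented in both arms under the same rule, the within-stratum difference is zero to within simulation error.
- The overall arm comparison is unbiased in every scenario.
- At 50% v 30%, a true difference of −26.45 mL appears as about −17.8 to −23.5 mL within strata.

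The positive sign means more contrast with navigation, so in these scenarios the distortion works against the system. It would reverse if navigation raised the stent rate.

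**4. Against sampling error.** With 80 per arm and 50% v 40% stented, the stented stratum holds 40 and 32 patients. SE ≈ 55.27 × √(1/40 + 1/32) = 13.1 mL, and the 95% half-width is 1.96 × 13.1 ≈ 26 mL. A bias of 1.6 to 4.0 mL is 0.12 to 0.31 of an SE.

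**The case against.** The strongest reply is that bias is possible but not shown. No section says that navigation changes stenting; the article describes stenting when indicated, and a system that helps reach the target. If allocation alters neither device use nor who receives devices, the within-stratum comparison is unbiased. This stands. A reader might infer that these subgroup results are bound to be biased, and the documents do not support that. Equal stent rates alone would not settle the matter, however, since different patients could be stented in each arm.

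A reader might also infer that the plan uses one of its own outcomes as a subgroup factor. That goes too far. Consumables per lesion is not defined and need not equal the number and type of devices placed per patient. It is a related quantity, and noting the influence on it makes an effect on device use plausible on the plan's own terms, no more.

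The magnitude is hypothetical. The stent rates and correlations have no source in the documents, and the largest figures need complexity to determine stenting completely. In the milder scenario the bias is small beside sampling error. The claim that a real effect would be hidden is not shown either: a true −26.45 mL is attenuated, not removed.

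Finally, these are additional analyses, the article states no causal reading of them, and an analysis plan not shown may say more. That limits the severity but does not answer the point. The protocol itself fixes this factor, and calling an analysis additional does not turn a stratum formed after randomisation into a randomised comparison.

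**Conclusion.** The point holds in a limited form. The device-use subgroups are formed after randomisation by an unblinded surgeon's decisions. Arm comparisons within them are open to bias if allocation changes device use or its recipients, and should not be read as randomised comparisons. This follows from the order of events alone.

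The size depends wholly on assumptions. It is zero if device use is unaffected, about 1.5 to 8 mL with a loose link between complexity and stenting, and up to about 14 mL at the extreme. The 26.45 mL used for scale is the superiority margin. It should not be taken for the plan's expected effect, which is 53.46 mL.

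Nothing here touches the primary intention-to-treat comparison, nor subgroups by indication or by lesion location recorded before the procedure. The change should be made, but the trial's main conclusion does not depend on it.

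**What to change.** In the section on additional analyses, remove devices used and placed from the subgroup factors. Report the number and type of devices by arm as a descriptive outcome, next to consumables per lesion. Limit subgroup factors to those recorded before randomisation, namely indication/diagnosis and lesion location from pre-procedure information, and assess each with a treatment-by-subgroup interaction. Site is not in the current list; adding it would be optional and is not needed to resolve this point.

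The cost is one sentence, and no data are lost. The trade-off is that no arm comparison within levels of device use would be reported. One practical check is needed: the timeline table does not show lesion location among the screening items, so confirm that a pre-procedure value is available, including for patients already enrolled. Recruitment is planned to run until October 2026, so the wording can be settled before analysis.
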